# Blended care vs. usual care in the treatment of depressive symptoms and disorders in general practice [BLENDING]: study protocol of a non-inferiority randomized trial

**DOI:** 10.1186/s12888-017-1376-1

**Published:** 2017-06-13

**Keywords:** eHealth, Blended care, Internet-based treatment, Depression, Depressive symptoms, Depressive disorders, General practice, Primary care, Effectiveness, Cost-effectiveness

## Abstract

**Background:**

The majority of patients with depressive disorders are treated by general practitioners (GPs) and are prescribed antidepressant medication. Patients prefer psychological treatments but they are under-used, mainly due to time constraints and limited accessibility. A promising approach to deliver psychological treatment is blended care, i.e. guided online treatment. However, the cost-effectiveness of blended care formatted as an online psychological treatment supported by the patients’ own GP or general practice mental health worker (MHW) in routine primary care is unknown. We aim to demonstrate non-inferiority of blended care compared with usual care in patients with depressive symptoms or a depressive disorder in general practice. Additionally, we will explore the real-time course over the day of emotions and affect, and events within individuals during treatment.

**Methods:**

This is a pragmatic non-inferiority trial including 300 patients with depressive symptoms, recruited by collaborating GPs and MHWs. After inclusion, participants are randomized to either blended care or usual care in routine general practice. Blended care consists of the ‘Act and Feel’ treatment: an eight-week web-based program based on behavioral activation with integrated monitoring of depressive symptomatology and automatized feedback. GPs or their MHWs coach the participants through regular face-to-face or telephonic consultations with at least three sessions. Depressive symptomatology, health status, functional impairment, treatment satisfaction, daily activities and resource use are assessed during a follow-up period of 12 months. During treatment, real-time fluctuations in emotions and affect, and daily events will be rated using ecological momentary assessment. The primary outcome is the reduction of depressive symptoms from baseline to three months follow-up. We will conduct intention-to-treat analyses and supplementary per-protocol analyses.

**Discussion:**

This trial will show whether blended care might be an appropriate treatment strategy for patients with depressive symptoms and depressive disorder in general practice.

**Trial registration:**

Netherlands Trial Register: NTR4757; 25 August 2014. http://www.trialregister.nl/trialreg/admin/rctview.asp?TC=4757. (Archived by WebCite® at http://www.webcitation.org/6mnXNMGef)

**Electronic supplementary material:**

The online version of this article (doi:10.1186/s12888-017-1376-1) contains supplementary material, which is available to authorized users.

## Background

Depressive disorders are common. Up to 15% of people in high-income countries experience a major depressive episode at least once in their lifetime [1, 2] Depressive disorders cause high personal and economic burden of disease through their effects on many aspects of life such as participation and functioning [3–5]

The majority of patients (65% to 80%) with mild and moderate depression are treated by general practitioners (GPs) [6–11]. GPs in many countries including the Netherlands are recommended to use a (collaborative) stepped care management approach in the treatment of depression with antidepressants appearing only in the second step [12, 13]. Nevertheless, in routine general practice an estimated 70% of cases are primarily treated with antidepressants worldwide [9, 14–16]. This is worrisome as there is increasing evidence that antidepressants, while bringing about side effects, are ineffective in patients with mild to moderate depressive disorders which are particularly common in general practice [17–19]. This contrasts with psychological treatments that have convincingly shown effectiveness in these patients [20]. Moreover, most patients prefer psychological treatment [21].

Clear barriers for the implementation of psychological treatment in general practice exist. First, most GPs have too little time and experience to offer psychological treatment themselves [22, 23]. Second, referral for psychological treatment is hampered by limited accessibility due to practical barriers, such as high costs of treatment, limited availability of trained professionals and transportation issues [22, 24, 25]. Next, patients may experience emotional barriers such as feared stigmatization [26].

Referral by GPs to web-based programs for the treatment of depression circumvents these problems effectively by providing direct availability of psychological treatment at home. Several systematic reviews demonstrated the effectiveness of online psychological treatment in the treatment of depression [27–29]. Interventions without therapist guidance, however, showed small mean effect size and low adherence. In contrast, web-based interventions guided by a therapist (blended care) displayed relatively large mean effect size and better adherence [27–29], even comparable to face-to-face psychological treatment [30, 31]. Better adherence to treatment is important also for psychological interventions, as it is associated with greater response to treatment [32]. Therefore, guidance seems essential in the online treatment of depression. Importantly, it can be delegated to less trained or less experienced professionals (i.e. task-sharing) [33].

In previous trials on blended care in general practice, experienced professionals such as clinical psychologists or psychiatrist guided the patients [34–42]. In none of these studies were participants guided by their own GP or mental health worker (MHW). This may impair the generalizability of the results of these studies to Dutch general practice or similar settings. MWHs support primary care in delivering good quality mental health care by providing brief and simplified psychological treatment, blended care or self-help [43, 44]

In previous studies mainly online psychological interventions based on cognitive behavioral therapy (CBT) have been studied [38, 42, 45–47]. In a recent study behavioral activation has been shown as effective and more cost-effective compared to CBT [48] and it has been experienced as less complicated and more accessible to patients and therapists [49]. MHWs can learn this technique relatively quickly and its effectiveness is comparable to behavioral activation delivered by more specialist staff with more training [49]. Therefore in this trial we evaluate a blended behavioral activation treatment (guided ‘Act and Feel’ treatment).

Blended care has been expected to reduce costs, because part of the psychological treatment is provided online. However, a limited number of studies assessed the cost-effectiveness of blended care in general practice [50, 51].

To our knowledge, this is the first study investigating the effectiveness and cost-effectiveness of a blended behavioral activation treatment for depressive symptoms and disorders as performed in routine general practice.

## Methods

### Study design and aims

This study is a pragmatic, two-arm non-inferiority randomized controlled trial with an economic evaluation in general practice. The primary aim is to study the short-term (i.e. three months) effectiveness of a blended behavioral activation treatment compared to care as usual (CAU) for patients with depressive symptoms or disorders in general practice. Secondary aims include the short- and long-term (i.e. 12 months) cost-effectiveness and effects of blended care on daily activities, treatment satisfaction, medication use and other related resource use. In addition, we will explore the effects of the blended behavioral activation treatment and CAU on the course of real-time experiences of emotion, affect and events over the day.

### Participants

Adults (18 years or over) with a GP diagnosis of depressive symptoms or a depressive disorder for whom the GP considers a next step in the treatment of depression will be included [12]. Patients who fulfill the following criteria will be excluded: a) severe depression requiring prompt referral to specialized mental health service according to the GP (e.g. acute suicidality); b) current/past severe mental illness: schizophrenia, psychotic episode, bipolar disorder, depression with psychotic features; c) current anxiety disorder as primary diagnosis; d) current substance abuse (alcohol, drugs); e) current psychological treatment for depression; such as (online) cognitive behavioral therapy; f) no access to internet; g) insufficient computer skills; h) insufficient proficiency of Dutch language.

### Study setting and recruitment

This trial will be conducted in approximately 45 general practices in the Netherlands, located both in cities and in villages. This is a closed trial, i.e. GPs and MHWs recruit participants among their registered patients only. Informed consent will be obtained from each patient. Baseline assessments include the Structured Clinical Interview for DSM-IV disorders I (SCID-I). Modules A (mood episode), D (mood disorders) and F (anxiety disorders) allowing for diagnosing depressive disorders and anxiety disorders. The before-mentioned exclusion criteria are verified using the screening questions of the SCID-I; if screened positive than the total concerning section is administered. A trained interviewer telephonically conducts the SCID. Agreement between telephonic and face-to-face assessment is excellent (90% agreement) [52].

### Randomization

#### Sequence generation and allocation

After baseline assessment participants are 1:1 randomly assigned to one of the treatment groups, stratified by sex, diagnosis (depressive symptoms or depressive disorder) and general practice (availability of a MHW). The randomization sequence is computer-generated with randomly varying block sizes and is concealed by an independent research department. After randomization, the researchers inform the general practice about the treatment allocation. The GP/MHW shares this information with the participant during the follow-up consultation. This trial is single-blinded, i.e. the treatment allocation is concealed from the outcome assessor and participants are asked not to reveal the treatment allocation (Fig. 1).

### Guided ‘act and feel’ treatment

The guided ‘Act and Feel’ treatment is an online self-management program blended with direct contacts (face-to-face or telephonic) with a MHW [53, 54]. The content of Act and Feel is based on the face-to-face behavioral activation by Lewinsohn [55] and focuses on depressive symptoms. Behavioral activation is based on the behavioral theory stating that depressive behavior is a consequence of low rates of response-contingent positive reinforcement [55]. Therefore, behavioral activation concentrates on activating individuals by increasing activities that are potentially reinforcing for the individual. ‘Act and Feel’ consists of eight modules with integrated monitoring of depressive symptomatology (including suicidality) and automatized feedback in a secure online environment. First, it provides psycho-education about depression and the rationale behind behavioral activation. Second, participants are given insight in their daily mood and behavior/activities using daily activity mood monitoring. Preplanned potential pleasurable activities are mood-independent increased to increase the sense of satisfaction and enhance mood in the long term. There is additionally attention for the role of avoidant behavior in depression and how to turn this to proactive behavior. Finally, it concludes with the development of a personal relapse prevention strategy.

Every module has a fixed structure, starting with a visual analogue scale (VAS) mood assessment (on a Likert scale from 1 to 10); the rationale of that module and specific exercises and it concludes with a summary and evaluation of that module. The ‘Act and Feel’ treatment provides automatically produced graphs of self-ratings mood score and depressive symptomatology.

#### Guidance

The MHW supports the participants with consultations of a targeted 30 min at two, four and six weeks. The purposes of these consultations are to motivate and support the participants during the activation process and to enhance adherence. In addition, participants receive e-mail reminders when inactive on the online environment for two weeks. The MHWs who guide Act and Feel follow a one-day training session on guidance of Act and Feel and behavioral activation and on-demand supervision of cases by the psychologist research assistant. Before implementation of this treatment, the usability of the ‘Act and Feel’ treatment was evaluated in a pilot study with twenty healthy volunteers. By means of this feedback the treatment was adjusted and after adjustment retested in a second pilot.

### Care as usual

The control group receives CAU for depression, left at the discretion of the GP. Patients with depressive disorders in routine usual general practice care are offered mostly pharmacological treatment and receive alongside some psychological treatment, such as non-directive counseling [56, 57]. We will not interfere with CAU but document it carefully. Nevertheless, GPs (or delegated to the MHW) are asked to plan consultations (telephonic or face-to-face) with the participant at two, four and six weeks as recommended by the guideline of the Dutch College of GPs thus mirroring the intervention arm [12]. In addition, patients are monitored for depressive symptomatology and acute suicidality.

### Concomitant treatments

Given the trial’s pragmatic nature, the aim is to quantify the real life difference in the course of depressive symptoms between blended behavioral activation and usual care. Consequently, all participants in both arms are allowed to continue or to start any medical or non-medical concomitant treatment, except for psychological treatment, which we ask not to offer in the intervention group during the first three months. For both groups, the use of all forms of formal health care during the trial is carefully documented.

### Participant timeline and assessments

Both clinical and economical outcomes are measured (Table 1). Interviewer-rated assessments are performed telephonically (i.e. SCID-I and HRSD-17) and the online self-report assessments through an online environment (ResearchOnline®). Follow-up assessments are at 3, 6 and 12 months.

**Table 1 Tab1:** Overview of the follow-up assessments of the participants

Measures	Description	Baseline	Week 1–10	3 months	6 months	12 months
HRSD-17	Depressive symptom rating	X		X		X
EMA	Daily real time ratings of emotion, affect and events		X			
SCID-I	Diagnosis of current depressive disorder	X				
QIDS-16	Depressive symptoms rating		X			
WHODAS-II	Functional impairment and activity limitation	X		X		X
EQ-5D	Health status	X		X		X
Daily activity section of Leidsche Rijn Health Questionnaire	Regular daily activities	X		X		X
Treatment satisfaction				X		X
TIC-P	Direct and indirect costs			X	X	X
Demographics	Socio-demographic characteristics	X				
Resource use	Medication use, number of referrals and GP consultations					X

HRSD-17: Hamilton Rating Scale for Depression, 17 items

EMA: ecological momentary assessments

SCID-I: Structured Clinical Interview for DSM disorders

QIDS-16: quick inventory of depressive symptomatology, 16 items

WHODAS-II: WHO Disability Schedule 2.0

EQ-5D: EuroQol five dimensions questionnaire

TIC-P: Trimbos and iMTA questionnaire on Costs associated with Psychiatric illness

GP: general practitioner

Random real-time assessments will be done in the first ten weeks of participation. In addition to the assessments, all patients are monitored for severe depression and acute suicidality by filling in the self-report questionnaire QIDS weekly during ten weeks.

### Outcomes

#### Primary outcome

The primary outcome is the reduction of depressive symptoms from baseline to three months follow-up, as measured with the Hamilton Depression Scale 17-items (HRSD-17) [58–60]. This is a clinician-rated scale consisting of 17 items. This scale has been widely used in clinical trials and serves as gold standard for assessment of depression. It has been found valid and reliable measurement outcome with a higher inter-rater reliability and test-retest reliability [59, 61].

### Secondary outcomes

#### Depression related outcomes

The reduction of depressive symptoms on the HRSD-17 is assessed from baseline to 12 months of follow-up. Additionally, response defined as a 50% reduction on the HRSD-17 is evaluated at 3 and 12 months. Furthermore, depressive symptoms are assessed weekly using the self-reported measurement Quick Inventory of Depressive symptoms self-reported 16 items (QIDS-SR 16). The QIDS-SR 16 are used to monitor depressive symptoms and to signal acute suicidality and severe depression during the first ten weeks of treatment. When exceeding the threshold of severe depression (i.e. HRSD-17 score 16 or higher) or acute suicidality (i.e. score of 2 or 3 on the suicidality item of the QIDS-R), all patients receives an automatic message to contact their GP and MHW and the researcher informs the GP.

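### The severe-depression alert is set on an HRSD-17 score, but the weekly checks it governs collect only the self-report QIDS-SR 16

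*Protocol article*

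**What the plan says.** Two sections name the QIDS as the monitoring instrument. Under Participant timeline and assessments: "all patients are monitored for severe depression and acute suicidality by filling in the self-report questionnaire QIDS weekly during ten weeks". Under Depression related outcomes: "The QIDS-SR 16 are used to monitor depressive symptoms and to signal acute suicidality and severe depression during the first ten weeks of treatment".

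The next sentence of Depression related outcomes states the alert rule, which has two limbs. The trigger reads "When exceeding the threshold of severe depression (i.e. HRSD-17 score 16 or higher) or acute suicidality", and the suicidality limb is then specified as "i.e. score of 2 or 3 on the suicidality item of the QIDS-R". If either limb is met, the patient automatically receives a message to contact the GP and MHW, and the researcher informs the GP.

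On the HRSD-17, Participant timeline and assessments says "Interviewer-rated assessments are performed telephonically (i.e. SCID-I and HRSD-17", in contrast to the self-report measures, which are completed online. Primary outcome also describes it as clinician-rated. Table 1 marks the HRSD-17 at baseline, 3 months and 12 months, and the QIDS-16 under weeks 1–10 only.

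**The concern.** The two limbs sit in one sentence, share one action and follow directly from a sentence about weekly QIDS signalling, yet only the suicidality limb uses a score that the weekly check produces. The severity limb asks for a score from an interview that is not held in that period.

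This is a safety rule. It decides when a patient is told to seek help and when the practice is informed. A patient whose depression becomes severe without a raised suicidality item depends on the severity limb alone to trigger the alert. If staff or programmers take the text literally, that limb never fires during the ten weeks. If they put in a QIDS cut-off of their own, the article does not tell them which value to use.

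**Working it through.** The check compares the alert rule with the assessment schedule. The article gives no figure to reproduce, and no power or error-rate calculation is involved.

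**Inputs**

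| Item | Value | Source |
|---|---|---|
| Monitoring window | weeks 1–10, weekly | Participant timeline and assessments; Depression related outcomes |
| Instrument completed each week | QIDS-SR 16, self-report | same sections; Table 1 |
| Severity limb | HRSD-17 of 16 or more | Depression related outcomes |
| Suicidality limb | QIDS item scored 2 or 3 | Depression related outcomes |
| HRSD-17 occasions | baseline, 3 months, 12 months | Table 1 |
| Planned consultations | weeks 2, 4 and 6 | Guidance; Care as usual |

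**Step 1: can each limb be evaluated at a weekly check?** Taking 3 months as 52/4 = 13 weeks, the HRSD-17 occasions are weeks 0, 13 and 52. None lies in weeks 1–10, so the severity limb has a score to act on at 0 of 10 checks. The QIDS is completed at each check, so the suicidality limb can be evaluated at 10 of 10.

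**Step 2: can the weekly data supply an HRSD-17 score another way?** The HRSD-17 is an interviewer rating and the QIDS an online self-report. The article gives no conversion between them and no QIDS total that denotes severe depression, so the intended weekly cut-off cannot be recovered from the text. Two readings remain open: 16 is a QIDS total with the wrong scale named beside it, or 16 is an HRSD-17 value to be translated into an unstated QIDS score.

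**Step 3: could the limb be meant for the scheduled interviews?** The first HRSD-17 after baseline comes at about week 13, which is 13 − 10 = 3 weeks after the last weekly check. On this reading the weekly monitoring for severe depression, promised in two sections, would have no threshold at all.

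**Step 4: what contact covers the gap?** For the blended arm, "The MHW supports the participants with consultations of a targeted 30 min at two, four and six weeks". In usual care, GPs or their delegated MHWs "are asked to plan consultations (telephonic or face-to-face) with the participant at two, four and six weeks". If the consultation weeks and QIDS weeks are counted from the same start, which the article does not state, consultations fall in 3 of the 10 weeks, and 4 of the 10 checks (weeks 7–10) come after the last planned one. The Abstract specifies at least three sessions in the blended arm, so later contacts there are possible but not scheduled.

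**The case against.** The strongest reply is that this is a slip of wording. Two sections fix the QIDS as the instrument, and an automatic message most naturally follows from an online questionnaire, so the running system probably already uses a QIDS score. On this view the parenthesis only anchors the idea of severe depression on the trial's main scale, and the QIDS equivalent is operational detail that an article may leave to the full protocol.

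Much of this is fair. The QIDS is very probably the intended instrument, and nothing in the article shows that the software is wrong. But the article does not merely leave a detail out: it states a specific threshold on a specific scale, and that statement conflicts with its own schedule. Recognising the slip does not settle the cut-off either, because both readings of 16 remain open.

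A second reply is that other safeguards exist, and this also stands. Act and Feel, an eight-week program, has built-in symptom and suicidality monitoring with automated feedback, so cover in the blended arm extends past week 6. Care as usual states that its patients are monitored for symptoms and suicidality, though this may be the same weekly QIDS. Patients whose severe depression needs prompt referral, in the GP's judgement, are excluded at entry, and patients stay under their own practice. These points reduce the consequence of the error but do not supply the missing threshold. The week counts describe the schedule; they do not measure harm.

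**Conclusion.** The concern holds. The severity limb names a score that is available at 0 of the 10 weekly checks, and the article offers no QIDS cut-off or conversion in its place. The suicidality limb is sound at all 10 checks.

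The effect is confined to patients who reach severe depression without scoring 2 or 3 on the suicidality item. The article gives no basis for estimating how many that is. The 0 of 10 result rests on Table 1 and the stated mode of assessment. The count of checks after the last consultation also assumes a common starting week.

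This is an error in a stated safety threshold. The primary outcome, its analysis and the sample size do not depend on it. It should be corrected because the rule triggers clinical action.

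**What to change.** In Depression related outcomes, restate the severity trigger as a QIDS-SR 16 total-score cut-off. The clinical lead should confirm whether the value is 16 on the QIDS itself or the QIDS score taken as equivalent to an HRSD-17 of 16; if the latter, the conversion should be stated. The suicidality trigger stays as it is.

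Then check once that the online alert is programmed to the confirmed value. Past weekly scores need review only if the programmed rule turns out to be wrong.

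The cost is a one-line text correction and one programming check. No assessment is added, and neither the analysis nor the sample size changes.
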